## Abstract

**Background:**

Traditionally, patients with peritonitis Hinchey III and IV due to perforated diverticulitis were treated with Hartmann’s procedure. In the past decade, resection and primary anastomosis have gained popularity over Hartmann’s procedure and recent guidelines recommend Hartmann’s procedure in two situations only: critically ill patients and in selected patients with multiple comorbidity (at high risk of complications).

The protective stoma (PS) is recommended after resection with primary anastomosis, however its interest has never been studied. The aim of this trial is to define the role of systematic PS after resection and primary anastomosis for peritonitis Hinchey III and IV due to perforated diverticulitis.

**Methods/design:**

This DIVERTI 2 trial is a multicenter, randomized, controlled, superiority trial comparing resection and primary anastomosis with (control group) or without (experimental group) PS in patients with peritonitis Hinchey III and IV due to perforated diverticulitis.

Primary endpoint is the overall 1 year morbidity according to the Clavien–Dindo classification of surgical complications. All complications occurring during hospitalization will be collected. Late complications occurring after hospitalization will be collected during follow-up.

In order to obtain 80% power for a difference given by respective main probabilities of 67% and 47% in the protective stoma and no protective stoma groups respectively, with a two-sided type I error of 5%, 96 patients will have to be included in each group, hence 192 patients overall. Expecting a 5% rate of patients not assessable for the primary end point (lost to follow-up), 204 patients will be enrolled.

Secondary endpoints are postoperative mortality, unplanned reinterventions, incisional surgical site infection (SSI), organ/space SSI, wound disruption, anastomotic leak, operating time, length of hospital stay, stoma at 1 year after initial surgery, quality of life, costs and quality-adjusted life years (QALYs).

**Discussion:**

The DIVERTI 2 trial is a prospective, multicenter, randomized, study to define the best strategy between PS and no PS in resection and primary anastomosis for patients presenting with peritonitis due to perforated diverticulitis.

**Trial registration:**

ClinicalTrial.gov: NCT04604730 date of registration October 27, 2020. https://clinicaltrials.gov/ct2/show/NCT04604730?recrs=a&cond=Diverticulitis&draw=2&rank=12.

## Background

Up to 35% of patients treated for acute diverticulitis have a complicated disease such as purulent or faecal peritonitis (Hinchey III or IV) [1, 2]. However, the optimal strategy for the surgical treatment of peritonitis remains a subject of debate.

Traditionally, patients with peritonitis Hinchey III and IV due to perforated diverticulitis were treated with Hartmann’s procedure. In the past decade, resection and primary anastomosis have gained popularity over Hartmann’s procedure and recent guidelines recommend Hartmann's procedure in two situations only: critically ill patients and in selected patients with multiple comorbidity (at high risk of complications) [3, 4].

Although defunctionning stomas are recommended after resection with primary anastomosis, its interest has never been studied.

Protective stoma can effectively reduce the consequences of anastomotic leakage on clinical course but it also has its own morbidity. Theses complications cannot be neglected, and have been highlighted in several studies in rectal cancer; in addition its reversal requires a second operation which has been associated with more than 20% of morbidity [5–9].

Mengual-Ballester et al. reported a 45.9% incidence of ileostomy-related complications, including diarrhea, surgical wound infection, intestinal obstruction, rectorrhagia, enterocutaneous fistula, and anastomotic leakage [10].

Moreover, a protective stoma involves specific costs and can altere patient’s self-perception [11].

In the randomized trial “Diverti” [12] comparing Hartmann’s procedure vs resection and primary anastomosis, 15 of the 50 patients in the primary-anastomosis group were not protected. In this subgroup, mortality related to the operation was nil, and morbidity was only 26% (n = 4). In addition, severe complications (Clavien–Dindo III–IV) and global morbidity were significantly lower in the group of patients without protective stoma (0% vs. 23%, p = 0.042 and 27% vs. 67%, p = 0.01, respectively).

In the Ladies trial [13], patients operated with (n = 40) and without a protective stoma (n = 17) were also compared. No difference in overall morbidity (23.5% vs 45%, p = 0.15) and mortality (0 vs 7.5%, p = 0.55) was objectified, but patients without ileostomy had a significantly shorter median length of stay (7 vs. 11, p = 0.01).

These studies certainly have “selection biases”. Patients operated without protective stoma may have been “low risk” patients. However, the results appear very favorable.

Large scale studies do not exist and there is still debate as to whether or not defunctionning stoma should be performed routinely or should be avoided when possible [14].

Prospective randomized trials are needed to define the best strategy between PS and no PS in resection and primary anastomosis for patients presenting with peritonitis due to perforated diverticulitis.

## Methods

### Study objectives and design

This DIVERTI 2 trial is a multicenter, randomized, controlled, superiority trial comparing resection and primary anastomosis with (control group) or without (experimental group) PS in patients with peritonitis Hinchey III and IV due to perforated diverticulitis. Figure 1 summarize the design of the study.

**Fig. 1 Fig1:**
[figure not shown]
Study design of DIVERTI 2

The recruitment will last 36 months the duration of the study will be 48 months. This study is supported by a grant from the French Ministry of Health (PHRC-19-0229).

### Endpoints

The primary endpoint is the 1 year overall morbidity, i.e., the number of patients who develop at least one complication (medical or surgical) at the 12-month follow-up.

All complications occurring during hospitalization will be collected. Late complications occurring after hospitalization will be collected during follow-up.

A 12-month endpoint was chosen because 50% of patients will require stoma closure 3–4 months after emergency surgery. In addition, some complications related to the realization of a protective stoma can occurred in the long-term (incisional hernia for example).

Secondary endpoints are the 90 days mortality; number of re-admissions and re-operations (other than for stoma closure); Incisional Surgical Site Infections (SSIs); Organ/space SSIs; Wound disruptions; Anastomotic leaks; Operating time; Intensive Care Unit (ICU) length of stay; total duration of hospital stay; number of patients with a stoma at 12 months after initial surgery; quality of life (QoL) assessed by the Short Form Health Survey (SF-36) [15], the Gastrointestinal Quality of Life Index (GIQLI) [16] and the EuroQol Five-levels (EQ-5D-5 L) (i.e., utility values for health states) [17] at baseline 6, 12, 26 and 52 weeks after primary surgery. A 12-month cost-utility analysis, will be also performed. For patients benefiting from a restoration of continuity, the analyses will be performed on the cumulative data of the two interventions.

### Sample size

The calculation of the sample size is based on the results of DIVERTI trial [12], which evaluated the overall morbidity after protective stoma. The rate of patients with complications after protective stoma at 1 year was 67%.

We assume that the percentage of patients with complications in the protective stoma group of our study will be comparable to that of DIVERTI trial and we have based our calculation of the sample size on this information.

The sample size has been calculated with respect to Pearson’s chi-square test at two-sided 0.05 level to compare the proportion of patients with complications 12 months postoperatively between the two groups (protective stoma vs. no protective stoma).

In order to obtain 80% power for a difference given by respective main probabilities of 67% and 47% in the protective stoma and no protective stoma groups respectively, with a two-sided type I error of 5%, 96 patients will have to be included in each group, hence 192 patients overall.

Expecting a 5% rate of patients not assessable for the primary end point (lost to follow-up), 204 patients will be enrolled.

### Study population

Table 1 summarizes the inclusion and non-inclusion criteria.

**Table 1 Tab1:** Inclusion and exclusion criteria

Inclusion criteria	Exclusion criteria
∙ Age ≥ 18 years ∙ Patients operated for purulent or fecal peritonitis (Hinchey stage III and IV) secondary to perforated diverticulitis of the left colon and treated by resection with primary anastomosis ∙ Patient having read and understood the information letter and signed the Informed Consent Form ∙ Patient able to comply with the study protocol, in the investigator’s judgment ∙ Patient affiliated with, or beneficiary of a social security (health insurance) category	∙ Physical states that prevent patient participation (e.g. septic shock or multivisceral failure) ∙ Steroid treatment > 20 mg daily ∙ Prior pelvic irradiation ∙ Immunocompromised status ∙ American Society of Anesthesiologists grade IV ∙ Peritonitis secondary to perforated diverticulitis of the right colon ∙ Patient is a pregnant or breastfeeding (lactating) woman or intending to become pregnant during the study ∙ Person deprived of liberty by administrative or judicial decision or placed under judicial protection (guardianship or supervision)

Inclusion criteria are patients older than 18 years with purulent or fecal peritonitis (Hinchey stage III and IV) secondary to perforated diverticulitis and able to provide informed consent.

Before enrollment, all patients have clinical assessment and CT scan and are informed about the study. The diagnosis is confirmed during surgery. Exclusion criteria are physical states that prevent patient’s participation (e.g. septic shock or multivisceral failure) and failure to provide consent.

### Participating centers

Twenty French public academic and non-academic hospitals will ensure recruitment.

A convention with the Direction of Research and Clinical Innovation of Rouen University Hospital, have been signed by all participating centers for ethical approval before beginning patient inclusion.

### Ethics

This study is conducted in accordance with the principles of the Declaration of Helsinki and ‘good clinical practice’ guidelines.

This study was submitted to the national drug agency (ANSM) and to the ethics committee “Comité de Protection des Personnes (CPP) Sud-Ouest et Outre-Mer II”, a national Institutional Review Board which belongs to the “Agence Regionale de Sante Occitanie”, on September 10th, 2020 (File number: 2-20-070 id8921); it was approved after minor corrections. Prior to randomization, written informed consent will be obtained from all patients. A new CPP assessment must be obtained for all protocol changes.

### Randomization

The investigator verify the eligibility of the patient with respect to the inclusion and non-inclusion criteria. After the delivery of oral information regarding the study, written consent is collected (day of inclusion). Both strategies are explained to the patients before enrollment in the study, along with their pros and cons. Randomization is performed just before surgery, by an online randomization system. Participating surgeons are allowed to login to the secured DIVERTI 2-trial website, after filling out the randomization form immediate response with randomization number and type of operation is obtained. The randomization list has been established using random number tables with a 1:1 ratio by a statistician before the initiation of the study. Randomization is stratified by center.

### Intervention

The patients are selected from the emergency department of each center. The diagnosis is established by the surgeon investigator on clinical data and imagery.

All consecutive patients with generalized peritonitis due to perforated diverticulitis are routinely proposed inclusion in the study. The decision of a possible inclusion is made after surgeon-anesthesiologist consultation. It’s the same if the patient’s condition changes peroperatively (infarction for example), a new surgeon-anesthesiologist consultation may need to modify the attitude initially adopted to adapt to the new clinical state of the patient.

The diagnosis of the non-tumor nature of the perforation is based on probability arguments and intraoperative findings. It isn’t be possible to obtain histological certainty of benign lesions before the first therapeutic act. Proof of diverticular perforation is required in each patient file at the end of the initial hospitalization.

Sigmoidectomy is performed through a midline laparotomy or laparoscopically, according to the standard technique, with lateral to medial mobilization of the left colon and mobilization of splenic flexure [12]. Vascular ligations are performed close to the intestine. The rectosigmoid junction is exposed and transected with a stapler. Proximal section is performed on a healthy colonic segment. The anastomosis is performed on well-vascularized digestive segments, without tension, according to the habits of the surgeon investigator (mechanical or manual anastomosis; end to end or side to end). After instillation of saline into the pelvis, the anastomosis is tested by air insufflation through the rectum. Decisions to clean the colon intraoperatively, to place a drain, and to perform ileostomy or colostomy (control arm) are left to the discretion of the surgeon.

In the control arm, stoma closure is performed at least 3 months after the first operation and after performing a barium enema to check for the absence of fistula or stenosis at the level of the anastomosis. Surgery is performed with a trephine incision, but the type of anastomosis (whether end-to-end or side-to-side, hand-sewn or stapled) is not restricted.

All patients are examined at 6, 12, and 26 weeks after the initial surgery, in the surgical department where they were operated; a final study visit will be carried out 12 months (evaluation of primary endpoint) after surgery.

The parameters explored at medical examinations are: occurrence of complications and quality of life assessment.

### Statistical analysis

Primary and secondary endpoints will be analyzed on an intention to treat basis. Data will be described overall and by randomized intervention group (protective stoma or no protective stoma) using standard parameters, i.e., mean, median, standard deviation, range and interquartile range for quantitative variables, and frequencies and percentages for categorical variables.

The main outcome being dichotomous, i.e., complication after surgery (yes/no), Pearson’s chi-square test or Fisher’s exact test will be used as appropriate to compare the two intervention arms 12 months postoperatively. Point and (exact if necessary) 95% confidence interval estimates of the proportions of complications in each arm will be calculated.

Use of the unadjusted test will be complemented by an adjusted comparison using the logistic regression model in order to adjust for center and possible prognostic characteristics.

The same general approach as outlined above will be used for secondary dichotomous outcomes (e.g., reinterventions, wound disruption, anastomotic leak). Regarding quantitative outcomes (e.g., operating time, length of postoperative hospital stay), comparison between the two intervention arms will be performed using Student’s test (or Mann–Whitney’s non parametric test as appropriate).

Quality of life scores will be described at each visit and compared between intervention groups at baseline and longitudinally during the study period using mixed linear models for repeated measures.

The overall survival at 3 months after surgery will be estimated using Kaplan–Meier survival curves and comparisons will rely on the logrank test.

The usual two-sided 0.05 level will be used for intervention comparisons.

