#### Utility measure

QALY will be derived from the EQ5D-5L questionnaire. The EQ-5D-5Luestionnaire will be filled at 6, 12, 26 and 52 weeks after primary surgery. For patients benefiting from a continuity restoration, analyses will be performed on the cumulative data of the two interventions.

To avoid overestimating or underestimating patients’ utility, it will be estimated that this utility evolves in a linear way taking into account the time between each visit for each patient in the two groups.

Therefore, QALYs will be calculated as the utility × time interval between measures.

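### Quality of life is to be compared between arms at baseline, and the plan does not say how the baseline score enters the longitudinal model, which may cost precision

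*Protocol article*

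**What the plan says.** In the protocol article, Statistical analysis first provides for describing quality-of-life scores at each visit. It then adds that they will be "compared between intervention groups at baseline and longitudinally during the study period using mixed linear models for repeated measures". The section closes with "The usual two-sided 0.05 level will be used for intervention comparisons", which on its face covers the baseline comparison too.

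Endpoints schedules SF-36, GIQLI and EQ-5D-5L "at baseline 6, 12, 26 and 52 weeks after primary surgery". Utility measure says that the EQ-5D-5L questionnaire "will be filled at 6, 12, 26 and 52 weeks after primary surgery", with no baseline.

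On timing, Randomization says "Randomization is performed just before surgery, by an online randomization system". No section says whether the baseline questionnaires come before or after that step.

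Adjustment is mentioned once in Statistical analysis, for the dichotomous primary outcome: a logistic model "in order to adjust for center and possible prognostic characteristics". Nothing comparable is said for quality of life, and nothing rules it out.

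**The concern.** Description is already covered, so a comparison at baseline reads as a significance test. With randomised arms and a baseline taken before allocation, the null hypothesis of that test is true by design. A significant result would be a false alarm, and a non-significant one would not show that the arms are balanced.

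The more useful role of a baseline score is to explain variation in the follow-up scores. The article gives it no such role. A longitudinal comparison that leaves it out, or lets the baseline arm means differ freely, may have a wider confidence interval than necessary. The Discussion expects impaired quality of life in stoma carriers to be avoided and presents the trial as the first to evaluate the stoma's effect on it. The precision of this contrast therefore matters to a stated aim, although the endpoint is secondary.

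**Working it through.** **The plan's own figure.** The only design calculation is for morbidity: 67% against 47%, two-sided 0.05, 80% power (Sample size). With pooled variance and no continuity correction:

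n = [1.960·√(2·0.57·0.43) + 0.842·√(0.67·0.33 + 0.47·0.53)]² / 0.20² ≈ 95.0, which rounds up to 96 per arm.

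Then 96/0.95 = 101.05, so 102 per arm and 204 enrolled. This reproduces, and nothing below changes it. No power figure is given for quality of life.

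**The baseline test.** Three instruments are each tested at 0.05. If the tests are taken as independent (an assumption) and the null is true, the chance of at least one false imbalance is 1 − 0.95³ = 14.3%.

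**Precision of the average follow-up difference.** Assumptions, none of them from the documents: unit variance at every visit, correlation 0.5 between any two of weeks 6, 12, 26 and 52, and correlation r_b between baseline and each follow-up visit. Variances are per patient.

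- Unadjusted mean of four visits: (4 + 12·0.5)/16 = 0.625.
- Adjusted for baseline: 0.625 − r_b².
- Power, for an effect with 80% power unadjusted: Φ(2.802·√(0.625/V) − 1.960), where V is the adjusted variance.

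| r_b | Adjusted variance V | Reduction | Power |
|---|---|---|---|
| 0.2 | 0.585 | 6% | 83% |
| 0.3 | 0.535 | 14% | 86% |
| 0.5 | 0.375 | 40% | 95% |

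**Does it matter how baseline enters the model?** The table gives the variance of the 52-week contrast relative to the raw follow-up difference, from generalised least squares on five visits with equal correlation ρ between all pairs of visits.

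| Form | ρ = 0.3 | ρ = 0.5 | ρ = 0.7 |
|---|---|---|---|
| Baseline a response, arm means free, raw contrast | 1.00 | 1.00 | 1.00 |
| Same model, change from baseline | 1.40 | 1.00 | 0.60 |
| Baseline as covariate | 0.91 | 0.75 | 0.51 |
| Baseline a response, arm means equal | 0.91 | 0.75 | 0.51 |

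The last two rows are identical, so a model with equal baseline means loses nothing. With free means, neither contrast does as well as adjustment.

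**Dilution, under one specific form only.** Suppose a single arm effect is averaged equally over five visits, baseline included. A constant follow-up effect then shrinks to 4/5 of its size. The variance is (5 + 12·0.5 + 8·r_b)/25 = (11 + 8r_b)/25, which is 0.504 at r_b = 0.2 and 0.600 at r_b = 0.5. Power is Φ(2.802·0.8·√(0.625/variance) − 1.960), or 70% and 63%, against 80% on follow-up alone.

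**The case against.** The strongest reply is that the article does not say what the mixed model contains. How baseline enters is a detail usually left to a statistical analysis plan, which is not shown, and the planned model may already constrain the baseline means. That stands: the precision loss is possible, not established, and its range includes zero.

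A reader might infer that the plan tests baseline instead of adjusting for it. The text makes no such choice; it names no covariate for quality of life and excludes none. A reader might also infer that the arm effect is diluted by one visit in five. That needs baseline as an outcome visit and one arm effect averaged over all five visits. The article states neither, and its wording can equally be read as keeping baseline apart from the longitudinal comparison. With an arm × visit term, the follow-up contrasts are not diluted.

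Two further replies are fair. Chance baseline imbalance in an unadjusted contrast is ordinary sampling variation that its standard error already covers; it is not bias. And removing the baseline test changes no effect estimate. Neither makes the test informative, and neither gives the baseline score a stated use.

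The true-null argument also depends on timing that the article does not give. If questionnaires are completed after allocation, the null is not guaranteed and the score is not a clean covariate.

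**Conclusion.** The concern holds in a limited form. A baseline comparison between arms is written into the plan, and it is uninformative if baseline precedes allocation. The article names no use of the baseline score for adjusting the longitudinal comparison, so precision may be given up.

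Under the assumed correlations, the avoidable variance in the average follow-up difference is 6% to 40%, and it is zero if baseline means are already constrained equal. The documents do not support calling this a definite loss, a deliberate choice against adjustment, or a diluted effect. The 70% to 63% power applies only to a five-visit average arm effect.

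For EQ-5D-5L, Endpoints and Utility measure disagree on whether a baseline exists, so it is not certain that adjustment is possible for that instrument. The consequences are confined to secondary endpoints.

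**What to change.** 1. Replace the baseline comparison with a description of baseline scores by arm, without a test.
2. Specify the mixed model for weeks 6, 12, 26 and 52 with arm, visit, arm × visit, baseline score × visit and center. Alternatively, keep baseline in the response vector with arm means constrained equal, which also retains patients whose baseline score is missing.
3. Report the adjusted difference with its 95% confidence interval at each visit and averaged over follow-up.
4. State that the baseline questionnaires are completed before randomisation. If some were not, say so and do not treat those scores as a pre-randomisation covariate.
5. Reconcile Endpoints with Utility measure on whether EQ-5D-5L is collected at baseline.

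The cost is analysis wording. Endpoints already schedules the baseline questionnaires, so no new data are needed unless item 5 shows that baseline EQ-5D-5L is not being collected. The sample size stays as it is.

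### Mortality is compared only to 90 days or 3 months, about when control-arm stoma closure first becomes possible, so deaths after a planned closure largely escape the mortality comparison

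*Protocol article*

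**What the plan says.** All references are to the protocol article.

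- **Endpoints, mortality:** "Secondary endpoints are the 90 days mortality". No later mortality endpoint is listed.
- **Statistical analysis, survival:** "The overall survival at 3 months after surgery will be estimated using" Kaplan–Meier curves, with a logrank test between the arms. This is the only survival comparison described.
- **Intervention, timing of closure:** "In the control arm, stoma closure is performed at least 3 months after the first operation".
- **Endpoints, reason for the primary window:** "A 12-month endpoint was chosen because 50% of patients will require stoma closure 3–4 months after emergency surgery".
- **Endpoints, patients whose continuity is restored:** "the analyses will be performed on the cumulative data of the two interventions". This sentence comes directly after the one on cost-utility and is repeated under Utility measure.

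Follow-up ends with a visit at 12 months, where the primary endpoint (at least one complication) is assessed.

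**The concern.** The trial compares two strategies, and one of them includes a planned second operation. The primary endpoint recognises this: its 12-month window is justified by the closure expected at 3 to 4 months. The mortality comparison does not follow the same logic. It stops at about the first day on which closure may take place.

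A patient in the control arm who dies after a planned closure would then be missing from both the 90-day endpoint and the 3-month logrank comparison. The other strategy contains no planned closure, so the omission tends to flatter the stoma arm. What is at stake is whether a secondary endpoint is complete and fair to both strategies. The primary conclusion is not in question.

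**Working it through.** **1. The article's own figure.** It gives no number for mortality. Its sample size reproduces: a two-sided 5% Pearson chi-square test of 67% versus 47% with 80% power and no continuity correction needs 96 per arm (power 80.4%). With 5% not assessable, 96 / 0.95 = 101.05, rounded up to 102 per arm, or 204 in total. So 102 is the size of the control arm used below. Nothing in this point changes it.

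**2. The windows side by side**, with the initial operation as time zero (assumed, because the article does not state it):

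| Item | Section | Time from initial operation |
|---|---|---|
| Mortality endpoint | Endpoints | ends at 90 days |
| Kaplan–Meier / logrank | Statistical analysis | ends at 3 months |
| Control-arm closure | Intervention | starts at 3 months or later |
| Expected closure | Endpoints | 3–4 months |
| Final visit, primary endpoint | Endpoints, Intervention | 12 months |

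Three calendar months last 89 to 92 days. A closure done to protocol therefore leaves at most about one day at risk inside the 90-day window (90 − 89 = 1), and essentially none inside the 3-month window.

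**3. How many deaths could be involved.** The article gives no mortality after closure, so these inputs are assumptions:

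- Share of controls closed: 50% to 100%. The article's 50% of patients can be read as half of the control arm (51 patients) or, with 1:1 allocation, as half of the whole trial, which is the entire control arm (0.5 × 204 = 102). The range covers both readings.
- Mortality after closure: 0.5% to 2%.

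Expected deaths after closure = 102 × share closed × closure mortality:

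| Share closed | at 0.5% | at 1% | at 2% |
|---|---|---|---|
| 50% | 0.26 | 0.51 | 1.02 |
| 100% | 0.51 | 1.02 | 2.04 |

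The chance of at least one such death runs from 1 − 0.995^51 = 0.23 to 1 − 0.98^102 = 0.87.

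**4. Does the primary endpoint make up for it?** In part. A complication of closure within 12 months counts there, but as morbidity. The endpoint is also yes/no per patient, so a control who already had a complication and then dies after closure adds nothing further. The article expects 67% of controls to have a complication by 12 months. It does not say how many of those would occur before closure, so the size of this overlap cannot be derived.

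**The case against.** The case on the other side has several parts.

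- **Time zero is not named.** The survival sentence refers only to surgery, whereas the Intervention section specifies the first or initial operation when it means that. If the cumulative-data sentence covers mortality, it could mean postoperative mortality added up over both operations, which would bring closure deaths in. If it covers only cost-utility, as its position and its repetition under Utility measure suggest, no rule is broken and the point concerns the choice of window. This stands. A reader might infer that no closure death can ever be counted, but the text supports that only for protocol-timed closures measured from the initial operation.
- **The second operation is captured elsewhere.** The primary endpoint and the economic evaluation both run to 12 months. This stands, with the limit shown in step 4 above.
- **Late deaths are not confined to one arm.** The Endpoints section does not restrict re-operations or stomas at 12 months to controls. A patient allocated to no stoma may receive one later and have it closed. This stands: the asymmetry lies in planned closures only.
- **The numbers are assumed and small**, and the endpoint is secondary, one of many. This stands too. The mortality contrast in the Background (0 vs 7.5%, in 17 and 40 patients) does not help to size the effect. It is non-randomised, the article itself acknowledges selection bias, and no time window is given.
- **A 90-day measure is a legitimate early summary of the emergency operation.** Agreed. That is a reason to keep it, but not to have it as the only comparison.

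**Conclusion.** The point holds as a mismatch of time windows. Provided that time zero is the initial operation, deaths after a protocol-timed closure fall essentially outside both mortality comparisons, although the article chose 12 months for the primary endpoint because of that closure. The direction tends to favour the stoma arm. The size is about 0.3 to 2 deaths among 102 controls, and that range rests wholly on assumed closure rates and closure mortality.

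A reader might go further and conclude that the mortality comparison is materially biased or that the trial's conclusion is at risk. The article does not support that: the endpoint is secondary, the expected counts are small, late deaths can occur in either arm, and the primary analysis and N = 204 are untouched. It is a worthwhile improvement at very little cost. The timing of closure itself is not questioned here.

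**What to change.** 1. State in the Endpoints and Statistical analysis sections that mortality and survival are timed from the initial operation.
2. Add all-cause mortality at 12 months, in both arms, as a secondary endpoint.
3. Run the Kaplan–Meier and logrank analysis to 12 months, and keep 90-day mortality as the early summary.
4. State whether the cumulative-data sentence applies to mortality or only to the cost-utility analysis.
5. Confirm that vital status and date of death are recorded up to the 12-month visit. The article lists complications and quality of life as the parameters examined at visits, so collection of deaths to 12 months is likely but has to be inferred.

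The cost is a change of wording and, if item 5 shows a gap, a field in the case report form. No extra visit, patient or sample size is needed. The Ethics section requires a new committee assessment for protocol changes, so this is best combined with any other amendment.
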